**Grade 2-4 Adverse Events Reported in > 3% of TDF Recipients in Study 903 (0-48 weeks)**

| **Type of Event** | **TDF+3TC+EFV**  **(N=299)** | **D4T+3TC+EFV**  **(N=301)** |
| --- | --- | --- |
| **General** |  |  |
| Headache | 10 % | 11% |
| Pain | 7 % | 6 % |
| Fever | 5 % | 6% |
| Abdominal pain | 4 % | 8 % |
| Back pain | 4% | 3% |
| Asthenia | 3% | 5% |
| **Gastrointestinal** |  |  |
| Nausea | 5% | 6 % |
| Diarrhea | 6% | 6% |
| Vomiting | 3% | 6% |
| Dyspepsia | 3% | 2% |
| **Neurologic** |  |  |
| Depression | 7% | 5% |
| Insomnia | 4% | 6% |
| Abnormal dreams | 3% | 3% |
| Dizziness | 3% | 5% |
| **Respiratory** |  |  |
| Pneumonia | 3% | 3% |
| **Dermatologic** |  |  |
| Rash (includes pruritus, urticaria) | 15 % | 11 % |

At 48 and 96 weeks, 1% and 3% of TDF patients experienced a serum creatinine increase of at least 0.5mg/dl from their baseline level and 5% and 6% experienced hypophosphatemia, respectively (Appendix 1 and indicated in tables below).

**Incidence of Creatinine Elevations Detected in Study 903 Participants (0-96 weeks)**

| **Serum Creatinine** | **TDF+3TC+EFV**  **(N=299)** | **D4T+3TC+EFV**  **(N=301)** |
| --- | --- | --- |
| Grade 1 (> 0.5 from baseline) | 3 % | 2% |
| Grade 2 (2.1-3.0) | <1 % | 0 |
| Grade 3 (3.1-6.0) | 0 | <1% |
| Grade 4 (<1.0) | 0 | 0 |

**Incidence of Hypophosphatemia Detected in Study 903 Participants (0-96 weeks)**

| **Hypophosphatemia** | **TDF+3TC+EFV**  **(N=299)** | **D4T+3TC+EFV**  **(N=301)** |
| --- | --- | --- |
| Grade 1 (2.0-<2.2) | 3 % | 3% |
| Grade 2 (1.5-1.9) | 3 % | 2% |
| Grade 3 (1.0-1.4) | <1 % | <1% |
| Grade 4 (<1.0) | 0 | 0 |

Whole-body dual-energy x-ray absorptiometry (DEXA) scans among study 903 participants demonstrated greater percent decreases in bone mineral density (BMD) from baseline in the TDF arm (spine, -3.3% + 3.9; hip -3.2% + 3.6) compared to the D4T arm (spine, -2.0% + 3.5; hip -1.8% + 3.3). At 48 weeks 6% of 300 TDF arm participants and 2% of 300 stavudine participants met the definition for a decrease in BMD and 13% and 10% at 96 weeks, respectively. However, 25% of participants were already osteopenic at baseline and this data did not correlate with incidence of fractures (11 in the stavudine and 4 in the TDF arm) through 3 years of the study. Additionally, all fractures reported were traumatic, except for one in the stavudine arm which was a spontaneous compression fracture. Thus, the clinical significance of these decreases is unknown (Appendix 1) (21).

The study 903 toxicity results are comparable to the phase III study (910) in which long‑term follow up showed a low rate of adverse events or laboratory abnormalities leading to TDF discontinuation despite a mean patient treatment duration of greater than two years, and as long as four years in others.

Several small brief clinical studies have been performed among HIV uninfected persons (studies 909, 914, 919, 929, 930, 932, 939, 943, and 984). The studies among healthy persons were primarily conducted to examine the pharmacokinetics (PK) of tenofovir alone or in combination with other ART. They enrolled small numbers of participants and were conducted for a median of 24 days (range 10-99 days); none examined extended safety. Data pooled from two small trials including HIV‑infected persons (n = 17, studies 901 and 907) and healthy volunteers (n = 36, study 914) demonstrated no significant differences in tenofovir PK by HIV infection status, gender, age (age range 19 to 57 years) or body weight (range, 50 to 112 kg). Other studies confirmed the safety of TDF among persons who used methadone, oral anticontraceptives, or had impaired hepatic function, and established dosage guidelines for patients with moderate to severe renal impairment (Appendix 1).

### Efficacy

Several large randomized clinical trials among HIV-infected persons have demonstrated TDF to be effective at reducing plasma HIV-1 RNA concentrations (studies 907, 902) and comparable to other ART regimens (903) (21). TDF is active against some HIV-1 isolates that are resistant to zidovudine, didanosine, abacavir, and lamivudine, and against multinucleoside drug-resistant variants carrying the Q151M mutation within the reverse transcriptase. Virus susceptibility to TDF is enhanced with the presence of the M184V mutation (22,23). TDF selects for a K65R mutation in the reverse transcriptase along with some other antireretrovirals, e.g. abacavir, didanosine. The K65R mutation is associated with a 3-4 fold reduction in tenofovir susceptibility in vitro and reduces susceptibility to lamivudine (22,24,25). Fortunately, it appears this signature mutation develops infrequently. Studies of TDF-containing regimens in HIV-infected persons for up to 96 weeks demonstrated infrequent development of K65R (2-3%; the median time to development of the K65R mutation was 27 weeks) and many of these persons were taking other antiretrovirals that could have contributed to development of this mutation(21,25,26).

Given its strong potency and favorable resistance profile, two recent studies yielded surprising results of poor efficacy when TDF was used as part of a triple nucleoside combination (27,28). Both studies noted high rates of virologic non-response, 58% and 49%, respectively, among patients receiving TDF in combination abacavir and lamivudine. Genotypes from the non-responders’ isolates yielded a lone M184V mutation, the M184V + K65R mutation, or wild-type virus; no patient failed with an isolated K65R mutation. It is uncertain what contributed to the non-virologic response. Hypotheses include intracellular pharmacologic interactions, or low genetic resistance barrier to the drug combination.

### Clinical Experience

Over 153,000 persons have now received TDF in a clinical setting, and relatively few adverse events have been reported. Those reported include renal impairment, nausea, rash and weakness (29-34). Renal adverse events have been the most extensively documented. A number of cases of tenofovir-associated nephrotoxicity involving renal failure, proteinuria, renal tubular dysfunction with Fanconi’s syndrome, and diabetes insipidus have been described among patients using TDF (31-37). In many of these cases, possible contributing factors included other ART, underlying renal disease, and low body weight.

TDF’s potential for mitochondrial toxicity and the associated lactic acidosis as compared with other NRTIs appears to be low (38,39). Two case reports noted fatal lactic acidosis in patients using TDF (30,40), however both patients were also receiving ddI, and one patient had multiple medical problems (30). Elevations of creatine phosphokinase (CPK) have been seen in patients using TDF, however these elevations may be due to concomitant use of acyclovir and/or atorvastatin (29). Given the concomitant use of other medications, in many clinical situations, it is difficult to assess the role of TDF in contributing to the toxicity (30-32,34).

In general, clinical experience suggests that oral, once-daily TDF appears comparable to placebo for safety, has durable efficacy in HIV-1 naïve and treatment-experienced patients and is generally safe when used in combination with other antiretrovirals in HIV-infected persons. In addition, other small studies suggest that TDF may lower lipid levels (41). However, the long-term safety profile for healthy, HIV uninfected persons has not been established.

### Non-Human Primate Challenge Studies

Tenofovir has demonstrated potent antiviral activity in several challenge experiments conducted among non-human primates providing strong support for both the pre-exposure as well as post-exposure use of TDF in the prevention of retroviral infections. These animal studies investigated TDF’s potential protective effect in retroviral challenges involving intravenous, oral, and intravaginal routes of transmission.

In one of the landmark studies, researchers demonstrated that tenofovir prevented simian immunodeficiency virus (SIV) infection in rhesus macaques administered once daily tenofovir following SIV intravenous challenge. Treatment was initiated either 48 hours before, 4 hours after, or 24 hours after SIV inoculation and continued for up to four weeks. All animals administered tenofovir remained healthy and free of SIV, whereas control macaques became infected and died quickly (7). A second study also demonstrated protection from simultaneous oral SIV and intravenous simian/human immunodeficiency virus (SHIV) inoculations in newborn macaques administered a two-week course of tenofovir starting immediately after viral inoculation (42).

Subsequent studies noted that both the timing of treatment initiation and the duration of therapy appeared to be important for protection. Two studies demonstrated that 2 doses of tenofovir administered 4 hour before and 20 hours after oral SIV inoculation protected newborn macaques (8) and suggested that partial protection could be achieved with lower and fewer doses (9). However, other studies demonstrated that although protection was achieved with a 28-day course of tenofovir started 12, 24, or 36 hours after retroviral exposure (intravaginal or intravenous), efficacy was reduced if therapy was initiated at 48 or 72 hours post inoculation or with shorter durations of treatment (10,43). Thus, although the optimal timing of dosing and duration of therapy are unknown, this promising data in animal models merits further investigation of tenofovir as a potential agent in the prevention of HIV infection.

## Rationale for the Current Study

Current efforts among high risk populations have focused on behavioral strategies, encouraging the reduction in the number of sexual partners, monogamy, and consistent and correct condom use for the prevention of sexually transmitted HIV. However, despite many years of designing, testing, and implementing behavioral interventions in the United States, the rate of new infections in the US has remained elevated for the last ten years (47,48). It is clear in order to reduce the incidence of HIV, both effective biomedical and behavioral prevention strategies are needed.

TDF has been selected for investigation as PrEP agent because of its unique pharmacologic characteristics (single daily tablet, low incidence of side effects, striking anti-HIV potency, and favorable resistance profile) and encouraging primate data. Two large phase IIb studies are scheduled for implementation by Family Health International (FHI) and University of California- San Francisco (UCSF) among 2000 high-risk women in four countries (Cambodia, Ghana, Nigeria, and Cameroon) to demonstrate the safety and effectiveness of once daily oral TDF for the prevention of HIV infection (49,50). Another potential study phase IIb may occur among men in Malawi. A CDC phase II study will provide extended clinical and behavioral safety data for men who have sex with men (MSM) who are at risk of acquiring HIV infection. TDF tablets and placebo will be provided by the pharmaceutical study sponsor, Gilead Sciences. The phase II clinical trial will be conducted in compliance with the protocol, Good Clinical Practices (ICH/GCP), and the applicable regulatory requirements of the US.

The CDC study will assess both the extended clinical and behavioral safety issues among MSM. Clinical safety will be evaluated by the use of standard clinical trial adverse event reporting. Although TDF has an excellent safety profile, two body organ systems (renal and bone) may exhibit signs of long-term toxicity and will receive close clinical and laboratory monitoring and assessment during this study. Behavioral safety will be assessed through participant reporting of HIV risk behavior and perceptions of treatment assignment and TDF efficacy using self-administered computerized questionnaires and testing for sexually transmitted infections (STIs). Participants will be randomized to one of four study arms. Two arms will receive daily oral TDF or placebo for 24 months (immediate treatment). The other two arms will enroll participants who receive no study product for the first nine months and then will receive either TDF or placebo for the remaining 15 months of the study (delayed treatment). The presence of the immediate and delayed treatment arms will allow for comparison of HIV risk behavior between those receiving study product and those not receiving study product. All participants will receive regular HIV counseling and testing by trained counselors.

# STUDY OBJECTIVES

Purpose: To evaluate the use of oral daily TDF by MSM at risk for HIV infection to determine its potential suitability for further evaluation as a preventive intervention

Primary Objectives

To evaluate the extended safety and tolerability of daily TDF 300 mg use by HIV negative MSM through

1. clinical and laboratory adverse events
2. self-reported risk behavior

Secondary Objectives

1. To describe the incidence of HIV infections and to evaluate whether administration of oral TDF affects the genetic characteristic of HIV-1 breakthrough viruses
2. To evaluate participants’ adherence with daily TDF use
3. To evaluate social and behavioral effects associated with participation in this safety trial

# STUDY DESIGN

This protocol describes a randomized, double-blind, placebo-controlled three-site study to evaluate the safety and tolerability of daily oral TDF among HIV-1 negative MSM.

Four hundred healthy, HIV‑1‑negative MSM will be randomized to one of four treatment arms:

Group 1: TDF 300 mg po QD

Group 2: Placebo po QD

Group 3: No study product for 9 months, followed by TDF 300 mg po QD

Group 4: No study product for 9 months, followed by placebo po QD

Groups 1 and 2 will be referred to as the immediate treatment arms and will receive study product for the entire 24 months of the study. Groups 3 and 4 will be referred to as the delayed treatment arms, and will receive study product starting at 9 months and ending at 24 months, for a total duration of 15 months on study product. For the purposes of this study, a month is considered 30 days. Participants will be stratified by enrollment site.

Participants will be monitored for clinical safety using periodic physical examinations, adverse event reporting, and serial laboratory testing. Given the uncertainty regarding the clinical significance of whole-body duel-energy x-ray absorptiometry [DEXA] findings and their lack of correlation with other clinical data (e.g. fractures), SFDPH site participants will receive DEXA scans at screening and two follow-up visits (at 12 and 24 months in the immediate arm, at 9 and 24 months in the delayed arm), and at the time of study discontinuation, if at least 6 months has passed since the previous scan. Behavioral safety will be primarily assessed by comparing reported risk behaviors between the immediate (pill-groups 1 and 2) and delayed (no pill-groups 3 and 4) treatment arms and will be evaluated by the use of periodic risk behavior assessments via audio computer-assisted self interview (ACASI) and regular laboratory testing for HIV and sexually transmitted infections (STI) including syphilis, *Neisseria gonorrhoeae* (GC), and Chlamydia trachomatis (CT). Additionally, measurements of adherence will be evaluated to determine product acceptability.

Study Schema

R

A

N

D

O

M

I

Z

E

Daily TDF

Daily Placebo

No treatment for 9 months, then daily TDF

No treatment for 9 months, then daily Placebo

Site B

Site A

Site C

Anticipated Timeline

Months

|  | 0-6 | | 7-12 | | | | 13-18 | | | 19-24 | | 25-30 | 31-36 | | 37-42 | |
| --- | --- | --- | --- | --- | --- | --- | --- | --- | --- | --- | --- | --- | --- | --- | --- | --- |
| Screening/Enrollment |  | | | |  | |  | | |  | |  |  | |  | |
| On Study |  | | | | | | | | | | | | |  | | |
| Safety Reviews |  |  | |  | |  | |  |  | |  |  |  | |  | |
| Closeout |  | |  | | | |  | | |  | |  |  |  | |  |
| Analyses |  | |  | | | |  | | |  | |  |  |  | | |

# PARTICIPANTS

## Target Populations

To assess the extended safety of TDF among HIV negative MSM, study sites need to have access to male populations with definable and predictable risks of HIV-1 infection based on established seroincidence rates. The recently completed AIDSVAX B/B HIV vaccine phase III efficacy trial included MSM enrolled from 56 sites in the United States, and HIV seroincidence was 2.8% (51). Since high-risk women will be exclusively studied in the FHI and UCSF studies, they will not be included in this study.

## Number of Participants and Participant Selection

A total of 400 HIV-1 uninfected, healthy MSM are planned for enrollment in this study. Men who are not known to be HIV-1 infected but who are at-risk of HIV-1 infection through sexual activity will be screened for possible trial participation. Participants may be enrolled from pre-existing cohorts or may be newly recruited for this study.

In the screening period, all potential participants will have a brief medical history and a directed physical exam to ensure that they are healthy and meet all eligibility criteria, and to document all past and baseline chronic, clinically significant medical conditions that may be relevant to the interpretation of adverse events during the study. Eligible subjects will be randomized to one of 4 study arms 1) immediate daily TDF (300 mg) 2) immediate daily placebo 3) no study product for 9 months followed by daily TDF for the remainder of the study; or 4) no study product for 9 months followed by daily placebo for the remainder of the study. Those participants who prematurely discontinue study drugs will be asked to continue with the scheduled study visits and will not be replaced.

## Inclusion Criteria

Participants must meet all of the following inclusion criteria within 45 days prior to randomization, unless specified otherwise, to be eligible for study entry:

*General*

- Healthy biologic male (male at birth)
- 18-60 years of age
- HIV-1 negative by licensed, commercially available, FDA-approved whole blood rapid enzyme immunoassay (EIA) at screening and enrollment
- Reports any anal sex with a man in the last 12 months
- Able to understand and pass comprehension assessment questionnaire
- Able to understand and sign a written informed consent form, which must be obtained prior to initiation of study procedures
- Able to understand English

*Biologic criteria*

- Adequate renal function:
- Calculated creatinine clearance (CrCl)  70 mL/min according to the Cockcroft‑Gault formula:

Male: (140 - age in years) x (wt in kg) = CrCl (mL/min)
 72 x (serum creatinine in mg/dL)

- Hepatic transaminases (AST and ALT)   2x upper limit of normal (ULN)
- Total bilirubin  1.5 mg/dL
- Adequate hematologic function: (absolute neutrophil count  1,500/mm3; platelets  100,000/mm3; hemoglobin  9.5 g/dL)[[1]](#footnote-2)
- Serum amylase  1.5 x ULN
- Adequate biochemical profile: within normal limits for serum phosphorus, potassium, sodium, and calcium.
- Hepatitis B surface antigen negative
- Normal urine dipstick or urinalysis (UA)
- Negative glucose
- Negative or trace protein, and
- Negative hemoglobin

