### Pharmacokinetics

The pharmacokinetics (PK) of TDF has been specifically evaluated in seven trials (studies 901, 907, 909, 914, 919, 930, and 932). These studies demonstrated that the bioavailability of TDF is enhanced by administration with food, TDF is eliminated by both active tubular secretion and glomerular filtration, and the TDF serum half‑life of ~17 hours and intracellular half-life of 10-50 hours supports a once-daily dosing schedule. Following oral administration of 300mg of TDF to HIV-infected patients in the fasted state, maximum serum concentrations are achieved in 1.0 + .4 hours. Since TDF is eliminated by the kidneys, a dose adjustment is necessary for patients with significant renal impairment. The only significant drug interaction reported is with didanosine (Videx® EC, [ddI]) in which ddI systemic exposures increased when administered simultaneously with TDF (Appendix 2).

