# TREATMENT PLAN AND STUDY PRODUCT

## Treatment Plan

Participants will be assigned a participant number at the time of screening consent. Once eligibility has been confirmed, the site will be given a specific numeric identifier that corresponds to the product assignment. All screening and baseline tests and procedures must be completed prior to the receipt of the first dose of study product. Initiation of treatment with study product must take place within 24 hours after product dispensation.

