## Product administration

Each participant will be randomly assigned a unique ID number that corresponds to a pre-labeled, blinded, bottle of study product (TDF or placebo) tablets. At the enrollment visit for the immediate treatment arms and at the 9 month visit for the delayed treatment arms, participants will receive 37 tablets. They must return within 1 month after initial product receipt for a safety visit before receiving further study product. At the 1 month (immediate arm) and 10 month (delayed arm) visits participants will **have any returned pills re-dispensed and will** receive **an additional** 68 tablets. At subsequent quarterly visits, participants will receive 105 tablets.

Participants will be instructed to orally self-administer one tablet daily. The tablet should be swallowed whole. It is important to take the tablets regularly. Each dose should be taken as close as possible to twenty-four hours apart at the same time each day.

The participant will be counseled regarding signs and symptoms of toxicity and the importance of adherence. Two weeks and two months after the enrollment visit for the immediate arms and at 9.5 and 11 months for the delayed arms, participants will receive a phone call from study staff to assess any immediate problems. In addition, participants will be encouraged to call for any adverse experiences possibly related to study product, all serious adverse events, symptoms of acute retroviral infection or concerns regarding product adherence. Participants will be instructed to return unused study medication at each study visit and about the correct use of the MEMS® cap. Participants should not share or dispense study product to any other persons.

Dosage Modification

No modification of dosage will be allowed from this study. If a dose is forgotten, it should be taken as soon as remembered on that same day that it was missed. If a daily dose is missed, the participant should not double the dose the next day.

*Adherence Reminder Sessions*

Face-to-face adherence reminder sessions will take place at the initial product dispensing and each study visit thereafter. This session will include:

- The importance of following study guidelines for adherence to once daily study product
- Instructions about taking study pills including dose timing, storage, and importance of taking pills whole, and what to do in the event of a missed dose.
- Instructions about the purpose, use, and care of the MEMS® cap and bottle

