## Toxicity Management

All adverse events and abnormal laboratory values (excluding creatinine elevations and decreases in BMD) will be graded according to the NIAID DAIDS Toxicity Grading Scale (Table 1 - Appendix 7). Creatinine elevations will be managed using the Gilead NIAID modified toxicity scale (Table 2 – Appendix 7). Decreases in BMD for the subset of participants receiving DEXA scans will be managed as described in section 6.5. All other clinical and laboratory toxicities will be managed according to the toxicity algorithms detailed in Appendix 8. Any questions regarding toxicity management should be directed to the CRO Medical Monitor and the CDC Medical Officer.

Grade 1 and 2 Laboratory Abnormality or Clinical Event (excluding creatinine elevations)

Continue study product at the discretion of the site investigator.

Grade 3 Laboratory Abnormality or Clinical Event (excluding creatinine elevations)

- Unrelated to study product

For a grade 3 laboratory abnormality or clinical event, confirmed by repeat testing, study product may be continued at the discretion of the site investigator if the event is considered to be unrelated to study product.

- Possibly related to study product

For a grade 3 clinical event or laboratory abnormality, confirmed by repeat testing, of which toxicity is possibly related to study product, study product should be withheld until the toxicity returns to ≤ grade 1, at which point the participant can be re-challenged with study drug at the site investigator’s discretion.

If a toxicity recurs to ≥  grade 3 following re-challenge with study product, is confirmed, then study product should be permanently discontinued and participants monitored and managed according to local practice.

- Probably related to study product

For a grade 3 clinical event or laboratory abnormality, confirmed by repeat testing, of which toxicity is probably related to study product, study product should be discontinued and clinical management should be discussed with the CDC medical project officer or the CRO Medical Monitor.

If a grade 3 laboratory toxicity is not confirmed by repeat testing, it should be managed per algorithm for the new toxicity grade.

*Grade 4 Laboratory Abnormality or Clinical Event (excluding creatinine elevations)*

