For a grade 4 clinical event or laboratory abnormality confirmed by repeat testing, study product should be discontinued and participant monitored and managed according to local practice. The participant should be followed as clinically indicated until the event resolves to baseline, stabilizes, or is otherwise explained, whichever occurs first.

If a grade 4 toxicity is confirmed and is considered to be unrelated to study product, study product should be withheld until the event resolves to baseline. Study product can then be restarted at the discretion of the site investigator.

If a grade 4 laboratory toxicity is not confirmed by repeat testing, it should be managed per algorithm for the new toxicity grade.

*Creatinine Elevations*

For a grade 1 serum creatinine elevation (>.5 increase from enrollment level) confirmed by repeat testing, study product should be held until creatinine returns to within .3 mg/dL of enrollment level, at which point participant can be re-challenged with full dose of study drug. If a confirmed grade 1 toxicity reoccurs, study product should be permanently discontinued, and participant monitored until level returns to baseline or stabilizes.

For a grade > 2 serum creatinine elevation (serum creatinine > 2.1) confirmed by repeat testing, study product should be permanently discontinued, and participant monitored until level returns to baseline or stabilizes.

Relationship of adverse event to study product

The Investigator must determine the relationship of the AE to the study product. For each AE, an assessment of the relatedness to the test agent should be made using the following scale:

- Unrelated: Onset of the AE had no reasonable temporal relationship to administration of the study product or a causal relationship to administration of the study product is biologically implausible or the event is attributed to an alternative etiology.
- Possibly Related: Onset of the AE has a reasonable temporal relationship to study product administration and a causal relationship is not biologically implausible.
- Probably Related: Onset of the AE has a strong temporal relationship to administration of the study product that cannot be explained by the participant’s clinical state or other factors and a causal relationship is not biologically implausible.

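### The entry limits for creatinine clearance, phosphorus and urinalysis are not re-applied before the delayed arms' first dose at month 9; only looser hold rules and investigator judgment could stop a start

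*Protocol*

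**What the plan says.** Section 4.3 (Inclusion Criteria) opens with "Participants must meet all of the following inclusion criteria within 45 days prior to randomization". The limits that matter here are a Cockcroft-Gault clearance of 70 mL/min (the comparison sign is lost in the text; I read it as at least 70), electrolytes and phosphorus "within normal limits for serum phosphorus, potassium, sodium, and calcium", and urine negative for glucose and hemoglobin with no more than trace protein.

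Section 6.4 (Product administration) gives the delayed arms their first supply: "at the 9 month visit for the delayed treatment arms, participants will receive 37 tablets". It attaches no laboratory condition to that dispensing, but it does require a safety visit within one month before any further supply. Section 5.1 (Treatment Plan) adds "All screening and baseline tests and procedures must be completed prior to the receipt of the first dose of study product", and has product started within 24 hours of dispensing.

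On holding product, section 9.6 (Toxicity Management) says of grade 1 and 2 events other than creatinine: "Continue study product at the discretion of the site investigator". For creatinine: "For a grade 1 serum creatinine elevation (>.5 increase from enrollment level) confirmed by repeat testing, study product should be held". It also stops product permanently for a confirmed grade 2 or higher creatinine (about 2.1 mg/dL), and interrupts or stops it for confirmed grade 4 values. Section 6.11 lets the investigator suspend product for illness, toxicity or the participant's best interest.

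On dosing, the Pharmacokinetics section states "Since TDF is eliminated by the kidneys, a dose adjustment is necessary for patients with significant renal impairment", and 6.4 states "No modification of dosage will be allowed from this study".

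**The concern.** The sponsor judged a set of renal, phosphorus and urine limits necessary before exposing a healthy man to TDF. In the immediate arms the limits are met at most 45 days before the first dose. In the delayed arms nine more months pass, and the visible text does not ask whether they are still met. The kidney is one of two organ systems that the Rationale section singles out for possible long-term toxicity. The other, bone, does get a check tied to the month-9 start: a DEXA scan, at one site and if possible.

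Because the dose cannot be reduced, not starting or holding is the only protection for a man whose clearance has fallen. Starting the drug in a healthy man who already has an abnormality is also a different decision from continuing it through a mild one, and 9.6 is written for the second.

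**Working it through.** **Age of the qualifying laboratory results.** A study month is 30 days (section 3), so month 9 is day 270. Screening limits may be met up to 45 days before randomization.
- Delayed arms: 270 + 0 to 270 + 45 = 270 to 315 days before first dose. If the 7-day visit window runs both ways: 263 to 322 days.
- Immediate arms: at most 45 days.

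**Which rules could stop a month-9 start.** Chemistry, hematology and urinalysis are drawn at months 1, 3, 6 and 9 (6.8), so the data exist.
- 5.1 asks only that screening and baseline tests be completed. A delayed-arm man did that nine months earlier.
- The 9.6 creatinine rule is measured from the enrollment level, so it can be read to cover a man not yet on product. It needs a confirmed rise of more than 0.5 mg/dL, or a value of about 2.1 mg/dL.
- Confirmed grade 4 values can likewise be read to bar a start. Grades 1 and 2, and grade 3 events judged unrelated to product, are left to the investigator.
- 6.11 is investigator judgment.

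None of these reproduces the 4.3 limits.

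**How far clearance can fall without a creatinine hold.** Cockcroft-Gault clearance is (140 − age) × weight / (72 × creatinine). With age and weight fixed, a rise *d* from enrollment creatinine *c* brings clearance to 70 when entry clearance is 70 × (c + d)/c. Men who entered below that figure end under 70:

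| Rise d (mg/dL) | c = 0.8 | c = 1.0 | c = 1.2 |
|---|---|---|---|
| 0.1 | 78.8 | 77.0 | 75.8 |
| 0.2 | 87.5 | 84.0 | 81.7 |
| 0.5 | 113.8 | 105.0 | 99.2 |

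Illustrative men (age, weight and creatinine are assumptions):
- Age 55, 70 kg, 1.1 to 1.2: 85 × 70/(72 × 1.1) = 75.1; 85 × 70/(72 × 1.2) = 68.9.
- Age 50, 70 kg, 1.0 to 1.3: 90 × 70/(72 × 1.0) = 87.5; 90 × 70/(72 × 1.3) = 67.3.
- Age 60, 70 kg, 1.1 to 1.6: 80 × 70/(72 × 1.1) = 70.7; 80 × 70/(72 × 1.6) = 48.6.

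In each case the rise is 0.5 mg/dL or less and the value is below 2.1, so the creatinine rule is silent.

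**Phosphorus.** In the study 903 table, grades 1 and 2 span 1.5 to below 2.2 mg/dL. These values fail the 4.3 limit if the local lower limit of normal is at least 2.2 (an assumption), yet 9.6 leaves them to discretion. They occur without TDF: 3% + 2% = 5% of the d4T arm over 96 weeks. Those patients were HIV-infected and on combination therapy, so this is context and not a rate for this trial.

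**The case against.** A reader might infer that delayed-arm men start with no laboratory limit at all. The documents do not support that. The creatinine hold refers to the enrollment level, the permanent stop is an absolute value, and the grade 4 rule applies even to events judged unrelated. Words such as continue, re-challenge and restart presuppose a man already on product, but the rules can fairly be read to bar a first dose.

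A reader might also infer that a man just under 70 mL/min receives a dose he should not have. That is not shown either. The protocol calls for adjustment in significant renal impairment, gives no threshold, and nowhere equates a clearance just below 70 with it. The examples ending at 68.9 and 67.3 show that the entry limit is no longer met, not that the dose is wrong. Only the 48.6 case might raise that question, and it needs a man near the limit to rise by exactly 0.5 mg/dL while off drug with no investigator stepping in.

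Other safeguards are real. There is a telephone call at two weeks. The first supply is 37 tablets, and the safety visit with laboratory tests at month 10 comes before any more. Chronic renal disease is excluded, nephrotoxic drugs are barred throughout, and section 10.8 has safety data reviewed rapidly. Immediate-arm men with the same drift also stay on product under the same 9.6 rules. Finally, a dispensing check could sit in the appendices.

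These points narrow the concern without removing it. The mitigations act after the first dose or depend on judgment, and none re-applies the standard set for entry.

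**Conclusion.** The point holds in a limited form. In the visible text, the 4.3 limits for clearance, phosphorus and urinalysis lapse after randomization and are not re-applied 270 to 315 days later, when the delayed arms first receive product. A man outside those limits may begin TDF at the investigator's discretion, with exposure capped at 37 tablets before the next safety visit.

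The number of such men cannot be estimated from the protocol and is probably small. The conclusion rests on three assumptions: the clearance limit is at least 70, the 9.6 rules are read generously as applying before a first dose, and Appendices 3, 7 and 8 contain no month-9 check. This is a safety gap that is cheap to close. It does not threaten the TDF-versus-placebo comparison.

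**What to change.** In 6.4, before first dispensing in the delayed arms, require the most recent scheduled results (month 6, with month 9 reviewed on receipt) to meet the 4.3 limits for clearance (using a current weight), phosphorus and urinalysis. Defer dispensing, or hold product already dispensed, until an out-of-limit value has been repeated and is back within limits. The month-9 review is needed because, with a two-sided 7-day window, month-6 results are (270 − 7) − (180 + 7) = 76 to (270 + 7) − (180 − 7) = 104 days old by then.

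State that deferred or never-started men remain in follow-up. The ITT definition in 10.4 must change too. It requires at least one dose, whereas 10.1 analyzes enrolled men as randomized whatever number of doses they took. Left alone, it would drop men whom the new check keeps off product from the month 0-9 behavioral comparison. All randomized men should be included there, in line with 10.1.

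The cost is wording in two sections, a weight and a laboratory check at month 9, and a repeat draw for men out of limits, with no new scheduled visit. A few men would start late or not at all, some of them for transient minor findings, and would contribute less time on product. The decision to dispense is made before any product is taken and without knowledge of TDF or placebo, so it favors neither.
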